## Abstract

**Background:**

Chronic neck and shoulder region pain affects many people around the world. This study aims to compare the effectiveness of three 8-week meditation training programmes (each using a different meditation technique: Anapana, Body scan or Metta) on pain and disability in a patient population affected with chronic neck and shoulder region pain, with a usual care control group and with each other.

**Methods:**

This four-arm parallel clinic-level randomised controlled trial will be conducted with male and female patients aged 18–65 years, who are affected with chronic neck and shoulder region pain, and who attend one of four clinics held on four different days of the week in a single medical centre in the Colombo North region, Sri Lanka. Clinics will be considered as clusters and randomly allocated to intervention and control arms.

Data will be collected using validated questionnaires, clinical examinations and focus groups. To compare primary (differences in changes in pain (Numeric Pain Rating Scale) at 8 weeks) and secondary (differences in changes in pain, physical disability, range of movement and quality of life (SF-36) at 4 and 12 weeks) outcomes between groups, a two-way ANOVA will be used if data are normally distributed. If data are not normally distributed, a nonparametric equivalent (Kruskal-Wallis) will be used. Focus group transcriptions will be thematically analysed using the Richie and Spencer model of qualitative data analysis.

**Discussion:**

This is a four-arm trial which describes how three different 8-week meditation technique (Anapana, Body Scan, Metta) interventions will be implemented with adult patients affected with chronic neck and shoulder region pain. The effectiveness of each meditation intervention on the pain, physical and psychosocial disabilities of patients will be compared between groups and with a usual care control group. The results of this study will contribute to recommendations for future meditation interventions for chronic neck and shoulder pain.

**Trial registration:**

ISRCTN12146140. Registered on 20 August 2021.

**Supplementary Information:**

The online version contains supplementary material available at 10.1186/s13063-022-06873-x.

## Administrative information

The numbers in curly brackets in this protocol refer to SPIRIT checklist item numbers. The order of the items has been modified to group similar items.

## Introduction

### Background and rationale {6a}

People of all ages can be affected by neck pain [1]. Most patients with neck pain are also affected with shoulder region pain [2]. Due to difficulties in demarcating neck and shoulder region pain, many prevalence studies have considered these two regions together [3]. Bad neck posture while sleeping and carrying out activities of daily living are recognised as the main risk factors for neck pain [4]. In addition to physical factors, there is an association between chronic neck pain and psychosocial factors such as cognitive distress, anxiety and depression [1].

Techniques commonly used to manage neck and shoulder region pain include medications, physiotherapy, acupuncture, physical exercises and yoga [5]. Medications used in the management of musculoskeletal painful conditions are associated with an increased risk of allergic reactions, gastritis, ischemic heart disease, type 2 diabetes, cataract, nephropathy and osteoporosis [6]. Other treatment modalities such as physiotherapy, physical exercises and yoga can be associated with adverse effects, such as pain, swelling and soft tissue injuries [5], while techniques such as spinal manipulations, acupuncture and relaxation have not been associated with significant positive effects in the management of neck pain [7]. According to Monticone and colleagues [1], cognitive behavioural therapy has not been associated with significant positive improvements in levels of neck pain. Hence, there is scope for treatment methods, such as meditation, which are safe, cheap to implement, and easily accessible.

In meditation, the person learns to take control of their emotions to become the master of their own mind [8]. There are many different types of meditation techniques. Anapana, Body scan and Metta are meditation techniques that are practised worldwide [9]. Available research suggests how meditation can be useful for managing painful conditions [10]. A randomised controlled trial (RCT) conducted by Colgan and colleagues [10] reported that meditation training can improve an individual’s ability to observe and experience internal reactions to a stressor as they arise, with acceptance, and equanimity. In turn, this impartial receptiveness can reduce emotional reactivity to the stressor [10]. A clinical trial conducted to investigate the effect of meditation on 48 patients, aged 30–45 years, suffering from lower back pain, demonstrated that meditation is useful in reducing pain and enhancing physical and mental quality of life, compared to usual care [9]. In this study, patients practised three different meditation techniques for 90 min a day, for 8 weeks. However, because the intervention group practised three different meditation techniques, it was not possible to differentiate the effect of the individual meditation techniques on pain relief and quality of life. Asking patients to practise three different meditation techniques in order to manage their pain might be overly burdensome outside of a research environment. Being able to make recommendations for one technique in isolation is more likely to be adhered to by patients, as a treatment for their pain management. Similarly, a home-based RCT with 89 patients with chronic neck pain demonstrated that Jyoti meditation significantly reduced pain at rest as measured by numerical pain rating scale compared to a physical exercise programme [11]. Jyoti meditation involves practising a combination of four types of meditation techniques, such as concentration on breath, sound, the flame of a candle and loving kindness [11]. Since Jyoti meditation involves practising a variety of techniques in combination, it is difficult to assess the effectiveness of one type of meditation on pain reduction. In a systematic review of the effectiveness of meditation interventions for the treatment of chronic pain, Magoline et al. [12] stated that they were unable to identify any head-to-head trials comparing different meditation interventions with regard to pain and quality of life.

To date, studies that have investigated the effectiveness of meditation on pain relief and disability have been conducted in countries outside of Sri Lanka. Included interventions have mostly involved lengthy meditation times that may not be feasible for working adults, ranging from 20 min/day [13] to 120 min/day [9]. To date, studies that have involved meditation sessions of a shorter duration, i.e. < 15min, have not shown significant benefits with regard to physical, psychological and social disabilities [14]. However, a descriptive analytical study conducted by Kabat-Zinn et al. [15] involving 90 patients with a variety of conditions (low back pain, headache, migraine, facial pain, abdominal pain and neck and shoulder pain) demonstrated that practising meditation for 15 min/day for 10 weeks was associated with significant reductions in pain, negative body image, mood disturbances and pain-related drug utilisation. In this study, 33% patients were affected with low back pain and 27% patients were affected with headaches. Since the patients falling into other disease conditions such as neck pain, shoulder pain, facial pain and abdominal pain were small in number, the clinical effect of meditation on those conditions cannot accurately be determined.

Patients have expressed the importance of having a meditation programme that is brief, is useful for everyday living and can be easily incorporated into their daily routine [16]. Sri Lanka is a developing country and many patients in Sri Lanka prefer traditional treatment methods that are low in cost and have minimal or no adverse effects [17]. Therefore, meditation might be a suitable treatment method to fulfil this need. No studies to date have compared the effects of different types of meditation techniques on patients affected with chronic neck and shoulder region pain. Therefore, there is justified scope to find out which type of meditation is more effective in the management of chronic neck and shoulder region pain, alongside a programme that could easily fit into patients’ daily routines. Thus, the present study intends to compare the effectiveness of three different mindfulness meditation techniques (Anapana, Metta and Body scan) practised over a short duration (15 min) daily for 8 weeks, with each other and a usual care group, for adult patients affected with chronic neck and shoulder region pain.

### Objectives {7}

[SPIRIT guidance: specific objectives or hypotheses.]To compare the effectiveness of three different meditation techniques:AnapanaBody scanMetta

with a usual care control group and with each other, at 4, 8 and 12 weeks’ follow-up on patients’ perceived neck and shoulder region pain, range of movement at the neck and shoulder and changes in physical and social disability relating to activities of daily living, occupation and social activities with family and friends.Explore how patients in each intervention group feel about the effectiveness of meditation for their chronic neck and shoulder region pain.

### Trial design {8}

This is a four-arm parallel group single-centre trial with a superiority framework. The following flow chart (Fig. 1) provides an outline of the stages of the trial. This study will be conducted in-line with the CONSORT statement [18] (Fig. 1).

**Fig. 1 Fig1:**
[figure not shown]
Flow chart to demonstrate the follow-up time periods

## Methods: participants, interventions and outcomes

### Study setting {9}

The study will be conducted in a rheumatology and family medicine clinic in Colombo, Sri Lanka.

### Eligibility criteria {10}

Study inclusion and exclusion criteria are described in Table 1.

**Table 1 Tab1:** Inclusion and exclusion criteria

Inclusion criteria	Exclusion criteria
• Patients affected with chronic (> 12 weeks) neck and shoulder region pain attending the four clinics managed by the same physician and physiotherapist.	Patients affected with infections, inflammatory arthropathies, malignancies, Alzheimer’s disease, psychiatric conditions, severe depression and anxiety will be excluded.
• Patients affected with mechanical causes such as degenerative changes of the spine, muscle strain, ligament sprain.	Patients who take part in yoga and other meditation programmes.
• Patients who can understand and communicate in Sinhala.	Patients who are below the age of 18 years and above the age of 65 years.

### Who will take informed consent? {26a}

The corresponding author will collect written informed consent from the participants after explaining the details of the study to them.

### Additional consent provisions for collection and use of participant data and biological specimens {26b}

No biological specimens will be collected, and there are no ancillary studies planned. Therefore, no additional consent will be obtained.

## Interventions

### Explanation for the choice of comparators {6b}

The present study intends to compare the effectiveness of three different mindfulness meditation techniques (Anapana, Metta and Body scan) practised over a short duration (15 min) daily for 8 weeks, with each other and a usual care group, for patients affected with chronic neck and shoulder region pain. Each different meditation technique will represent a different intervention in the trial. These three techniques are commonly practised worldwide.

### Intervention description {11a}

This study consists of three intervention groups and a control group. Each intervention group will be practising a different meditation technique for 8 weeks in addition to usual care. The control group will follow only usual care. Usual care entails medication (e.g. non-steroidal anti-inflammatory) and physiotherapy. Participants in the meditation intervention will also receive the usual care.

The three different types of meditation techniques are:Anapana (concentration on breathing)Body scan (concentration on bodily sensations without reacting to them)Metta (concentration on loving kindness) [19]

In Anapana meditation, the attention is on ‘the breath’ and it focuses on ignoring any distractions that might break the chain of awareness on ‘the breath’. It helps to keep away thoughts of cravings, aversions, fantasies and illusions [8].

In Body scan meditation, the meditator observes bodily sensations in a systematic manner from head to feet and from feet to head; by not reacting to them, it helps the meditator to realise the impermanent nature of these sensations, and consequently, this will help the meditator to get rid of thoughts of cravings and aversions [8].

Practising Metta meditation helps to remove thoughts of anger and hatred from the mind and introduce thoughts of patience, friendship and love [20].

The meditation techniques will be taught to the patients by a meditation trainer who has more than 10 years of experience in teaching meditation. Meditation techniques will be taught on a weekly basis for 8 weeks. Other than the teaching session, participants will be provided with a leaflet giving them instructions on the technique. Each session will include five patients and last for 30–45 min [9]. In between weekly training sessions, patients in the intervention groups will be requested to practise the meditation technique that was taught to them, for 15 min each day. They will be advised to only practise the meditation technique that was taught to them and not to practise any other technique. Participants will be requested and instructed to keep a logbook record of their daily meditation practice. Participants will also be requested to log the type, dose and amount of medication taken each day.

### Criteria for discontinuing or modifying allocated interventions {11b}

Participants will not be subjected to any pain or harmful interventions. Therefore, we do not feel that there will be a necessity to modify the allocated intervention.

### Strategies to improve adherence to interventions {11c}

Daily short message services (SMS) will be sent to participants reminding them to practise their allocated meditation and to complete their log book. Weekly face-to-face meditation training sessions with the meditation trainer will also be used to address any concerns or difficulties experienced by participants.

### Relevant concomitant care permitted or prohibited during the trial {11d}

Participants in the intervention groups will be asked not to take part in any meditation or yoga programmes other than their allocated meditation intervention. Participants in the usual care group will also be requested not to take part in any meditation programmes or yoga during the 8-week intervention period of the trial. Additionally, participants will be advised not to engage in treatment for their neck and shoulder region pain, other than from the physician or therapist in the registered clinic as part of the trial. Pharmacological treatments for pain, for example anti-inflammatory medications, will not be prohibited during the trial if they are part of usual care provided by the physician.

### Provisions for post-trial care {30}

No harmful procedures will be conducted during the trial. Therefore, it is unlikely that the participants will need post trial care. If by chance the participants need any care, they will be referred to the appropriate specialist.

### Outcomes {12}

Primary and secondary outcomes are stated in Table 2.

**Table 2 Tab2:** Primary and secondary outcomes

Primary outcome	Secondary outcomes
Differences in changes in pain in the neck and shoulder region at 8 weeks’ follow-up.	(i) Differences in changes in pain in the neck and shoulder region at 4 and 12 weeks’ follow-up.
	(ii) Differences in changes in the pain free active range of movement in the neck and shoulder region at 4-, 8- and 12-week follow-up.
	(iii) Differences in changes in quality of life with regard to activities of daily living, occupation and social activities with family and friends at 4, 8 and 12 weeks’ follow-up.
	(iv) To determine how patients in the three intervention groups feel about the effects of meditation on pain, physical and social disability with regard to activities of daily living, occupation and social activities with family and friends at 8 weeks’ follow-up.

Participants will be requested to report the pain intensity ratings from the previous 24 h using the Numeric Pain Rating Scale (range 0–10) [21] (Table 3) corresponding to:Pain level when they wake up in the morningLeast painWorst painWhile pain intensity was assessed three times across 24 h, the mean score across the three ratings will be used as the primary outcome.The pain intensity ratings need to be maintained daily.

**Table 3 Tab3:** Methods of measurement of outcomes

Outcome measure	Method of measurement
Level of pain	Numeric Pain Rating Scale, rated on a 0–10 scale [21]
Physical disability	Oswestry Neck Disability questionnaire [22], Disability of Arm, Shoulder and Hand (DASH) questionnaire [23], questionnaire to assess details of pain and demographic data, and clinical assessment of active range of movement of neck and shoulder joint [5]
Quality of life	The SF-36 Questionnaire Short Form [24]
Feelings on pain, physical disability and psycho social disability	This will be assessed qualitatively using focus groups.

Differences in quality of life will be assessed using the validated SF-36 questionnaire [24] (Table 3).

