### Participant timeline {13}

The duration of the trial is 12 weeks and the supervised intervention duration is 8 weeks. The participants will be assessed at baseline and 4, 8 and 12 weeks’ follow-up.

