### Sample size {14}

Sample size was calculated using the WinPepi version 11.65 statistical software. Results from a study by Jeitler et al. [11] with patients with chronic neck pain were used to calculate the sample size. In sample size estimation, we used the standard deviation values of the intervention group (17.2) and the control groups (21.5) after 8 weeks of treatment as stated in the study done by Jeitler et al. [11]. According to this study, the baseline pain value (45.5 SD 23.3) in the intervention group reduced to (21.6 SD 17.2) after 8 weeks of treatment and the baseline pain value (43.8 SD 22) in the control group reduced to (37.7 SD 21.5) after 8 weeks of treatment. Therefore, we considered 17.8 as the minimally important clinical difference. Using these values and a power of 80%, ratio of 1:1 and a significance level of 5%, the sample size was calculated. According to the calculation, the total sample size was 76 and number of patients for each arm of the trial was 19. According to an RCT conducted by Rantonen et al. [25] involving three intervention groups and a control group, the dropout rate was 26%. If we use this 26% dropout rate, and to maintain a total sample of at least 76, we need to have at least 26 patients per each arm of the trial. No adjustments will be made for multiple testing.

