## Statistical methods

### Statistical methods for primary and secondary outcomes {20a}

Descriptive statistics (means, SDs, percentages, *T*-tests, chi-square tests) will be used to describe patient characteristics at baseline, differences between groups at baseline, and for all outcomes at each follow-up time point (4-, 8- and 12-week follow-up). The significance level that will be used is 5% (corresponding 95% confidence intervals will be presented) [26] and the SPSS statistical soft wear version 21 will be used in data analysis. If data is normally distributed, a two-way ANOVA will be used to explore any changes in the primary outcome between patients in the three intervention arms (Anapana, Body Scan and Metta) and the usual care control group between baseline and the 8-week follow-up. Similarly, any changes in secondary outcomes between the four arms (three intervention arms and the control arm) will be explored at 4- and 12-week follow-ups. If the data is not normally distributed, a nonparametric equivalent, such as Kruskal-Wallis, will be used.

Treatment effects (between group differences) will be presented with corresponding confidence intervals.

Multivariate linear regression will be used to explore any effect of the independent variables of age, gender, level of income, level of education, changes in the amount of medication used and the weekly, mean meditation duration on the primary outcome at 8-week follow-up and in the secondary outcomes at 4- and 12-week follow-up. However, because they are not assessing differences between treatment arms, multivariate regression analyses will only be exploratory.

All focus groups will be audio-recorded and transcribed verbatim and translated to English [27]. For the qualitative data analysis, the literature recommends a scientific model be used [27]. To do this, the Richie and Spencer model will be used as it provides a sound analytical model [27]. ATLAS.ti will be used to manage the analysis due to its usefulness for coding.

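### Pain is rated daily, but the primary score is a single 24-hour mean with no stated day; a baseline-adjusted 7-day mean would be more precise at little cost.

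*Protocol article*

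**What the plan says.** The primary outcome in Table 2 is "Differences in changes in pain in the neck and shoulder region at 8 weeks’ follow-up". The text under that table describes the measurement: "Participants will be requested to report the pain intensity ratings from the previous 24 h using the Numeric Pain Rating Scale (range 0–10"), for pain on waking, least pain and worst pain. It then fixes the score: "the mean score across the three ratings will be used as the primary outcome". The next sentence adds: "The pain intensity ratings need to be maintained daily".

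Participant timeline {13} sets the visits: "The participants will be assessed at baseline and 4, 8 and 12 weeks’ follow-up". Statistical methods {20a} compares the arms by two-way ANOVA, or a nonparametric equivalent, on changes "between patients in the three intervention arms (Anapana, Body Scan and Metta) and the usual care control group between baseline and the 8-week follow-up". No section of the article averages the daily scores over days or says which 24 hours stand for week 8.

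**The concern.** Chronic pain varies from day to day. Averaging three ratings taken within one day does not remove that variation, whereas averaging several days does. If participants already record pain daily, a week of scores around each follow-up visit is available at almost no extra burden.

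The trial plans for 19 evaluable patients per arm, and its own Study limitations section lists the small number per arm. It also compares the techniques with one another. Avoidable day-to-day noise widens every one of those intervals. In addition, with no day fixed for the week-8 value, the choice of day stays open until the data are in hand.

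**Working it through.** **1. The plan's own figure.** Sample size {14} supplies the inputs: "we used the standard deviation values of the intervention group (17.2) and the control groups (21.5) after 8 weeks of treatment", and "we considered 17.8 as the minimally important clinical difference". It adds 80% power, a 5% significance level and a 1:1 ratio.

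- Common SD = √[(17.2² + 21.5²)/2] = √379.05 = 19.47.
- n per arm = 2 × [19.47 × (1.960 + 0.842)/17.8]² = 18.78, rounded up to 19; 4 × 19 = 76.
- Dropout: 19/(1 − 0.26) = 25.7, rounded up to 26.

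The stated 19, 76 and 26 all reproduce with a two-sided test, so the sample size is not in error on its own inputs.

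**2. Week-8 score, one day against 7 days.** Let r be the correlation between two days' scores in the same patient near week 8. The documents do not give it; I assume 0.5 to 0.9. Relative to one day, the variance of a 7-day mean is (1 + 6r)/7.

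| r | Variance ratio | Cut in variance |
|---|---|---|
| 0.5 | 4.0/7 = 0.571 | 43% |
| 0.7 | 5.2/7 = 0.743 | 26% |
| 0.9 | 6.4/7 = 0.914 | 9% |

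With only 4 rated days the ratio is (1 + 3r)/4, that is 0.625 at r = 0.5 and 0.925 at r = 0.9. Most of the gain survives some missing diary days.

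**3. Raw change score, averaging at week 8 only.** The primary outcome is a change, and the article does not say whether daily ratings exist before treatment. Set the single-day variance to 1, made up of a stable part r and day noise 1 − r. Let R be the correlation of the stable part between baseline and week 8, assumed 0.3 to 0.7.

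- Single day at both times: 2r(1 − R) + 2(1 − r).
- Single-day baseline, 7-day week 8: 2r(1 − R) + (1 − r) + (1 − r)/7.
- Largest gain (r = 0.5, R = 0.7): (0.300 + 0.500 + 0.071)/(0.300 + 1.000) = 0.871/1.300 = 0.670, a cut of 33%.
- Smallest gain (r = 0.9, R = 0.3): (1.260 + 0.100 + 0.014)/(1.260 + 0.200) = 1.374/1.460 = 0.941, a cut of 6%.

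**4. Baseline-adjusted analysis.** In the same model, adjusting for the single-day baseline removes (rR)² from the week-8 variance whether one day or seven are used. Taking the same amount from both cannot shrink the proportional cut, so the cuts in step 2 are a floor for the adjusted analysis. This is why adjustment suits a single-score baseline better than a raw change does.

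**The case against.** The strongest objection concerns the reading. A reader might infer that the plan discards the diary. The article does not say so; it only states no use for it. The three-rating mean could also be read as the score for each day, with the averaging window left to an unseen analysis plan. That is fair, and it limits the point. Still, the article itself defines the primary score and its 24-hour span, and on either reading no window or day is fixed.

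A reader might also infer that one missed diary day loses the outcome. The section on non-adherence and missing data {20c} points the other way, because outcome data are collected at clinic appointments. I do not rely on that argument.

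A third tempting step is to quote power. On the protocol's inputs, t-based power with 19 per arm would go from 78% to 95% at r = 0.5, or to 82% at r = 0.9. These are not this trial's power. The SDs come from another trial, whose values (for example 45.5 and 21.6) cannot lie on a 0–10 scale, and they are only assumed to be single-day SDs. The SDs are also those of week-8 values, while the outcome is a change. Allocation is by clinic day, and averaging over days does nothing to variation between clinic days. Only the relative gain carries over.

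The diary itself is not beyond doubt. The intervention description {11a} lists meditation practice and medication as logbook contents, not pain. The reminders in {11c} concern the allocated meditation and the logbook, and weekly trainer contact belongs to the meditation arms. Completion could therefore differ by arm, and a bare minimum-days rule could bring arm-dependent missingness into the primary outcome. This objection stands, and the fix has to guard against it. Nor does the article say that daily ratings continue to week 12.

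**Conclusion.** The point holds as an efficiency gain with safeguards. The article asks for daily ratings, builds the primary score from one 24-hour set, and names no day for week 8. A 7-day mean is more precise for any day-to-day correlation below 1.

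The size rests on assumed correlations: a 43% to 9% cut in the variance of the week-8 score for r from 0.5 to 0.9, or 33% to 6% for a raw change averaged only at week 8, with R from 0.3 to 0.7. Near r = 0.9 the gain is small. There is no bias and no error in the stated sample size. The change is worth making because it is cheap, not because the present plan is invalid.

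**What to change.** Before any by-arm data are seen, and in a dated amendment:

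- Define the week-8 pain score as the mean of the daily three-rating scores over the 7 days up to the visit. Do the same at week 4, and at week 12 if daily ratings run that long.
- Require a minimum number of rated days, for example 4. Where it is not met, use the visit's 24-hour score, so that no patient drops out of the analysis because of the diary.
- Compare arms with adjustment for the existing baseline score rather than on a raw change, since a 7-day follow-up mean and a single-score baseline do not form a like-for-like change.
- Keep the single-day score, with its day stated, as a sensitivity analysis.
- Report diary completion by arm.

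If an unseen analysis plan already sets a window, bring the article's definition into line with it.

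Costs: the primary definition changes after recruitment began (18 April 2022, under Trial status). The score depends on diary completion that may differ by arm. Data entry rises to up to 7 × 3 = 21 ratings per follow-up visit instead of 3.
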